### Screening and baseline assessment

The screening portion of the baseline assessment consists of demographic information, internalizing and externalizing symptoms, and post-traumatic stress. Screening instruments will be administered using the audio computer-assisted self-interviewing (ACASI) system. Participants can navigate through the questionnaires themselves using a laptop computer while listening to the questions through headphones and seeing the question and response options on the screen. A research assistant will be positioned nearby in case the participant has any difficulty. We have used ACASI extensively with AYA populations in Zambia and found it to be an acceptable and feasible approach for measuring mental and behavioral health outcomes [69]. All measures included in the ACASI have previously been used by our team with similar study populations and are available in English, Bemba, and Nyanja [35, 68–72].

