### Randomization and blinding

Each participant will be assigned a unique ID number by the research assistant during the screening/baseline assessment. Randomization will occur at the individual AYA level and be stratified by site. Following the determination of eligibility and completion of the baseline assessment, the research assistant will communicate the ID number to a study staff based at research headquarters who will not interact with study participants. This study staff will maintain a randomization sequence that will be developed a priori by a US-based research staff. This list will not be available or viewable to data collectors in Zambia. The list will have a sequence of treatment assignments (CETA or T-CETA or TAU) in random order, stratified by site, produced via a random number generator in Microsoft Excel. Randomization will be imbalanced (1.5 CETA: 1.5 T-CETA: 1 TAU) due to the different sample size requirements in the TAU control arm (see the “Data analysis” section). Eligible AYA participants will be assigned a condition based on the next available slot on the randomization list and inform the field staff of the assignment. At this point, the field staff will not be blinded to condition assignment for participants they assess. Eligible AYA clients will be informed immediately of the result of the randomization and appropriate next steps: CETA and T-CETA participants will be told that a counselor will be contacting them within 48 h to set up the first session; TAU participants will be told that the study team will contact them in approximately 3 months to schedule their first post-assessment. The use of ACASI will result in the outcome assessments being blinded; data analysts will also be blind to the intervention status when conducting analyses. Due to the nature of the intervention, neither counselors nor AYA clients will be blinded.

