## Discussion

Scalable systems of care, such as those being tested in this trial, are needed to close the mental health treatment gap in LMIC, particularly for populations at-risk for poor outcomes and low treatment adherence, such as adolescents and young adults. The need for telephone-based mental health services in LMIC has become widely discussed during the COVID-19 pandemic. Significant barriers to scale-up of evidence-based treatments in LMIC include a lack of feasible, sustainable training for local lay providers, and client access to care. This will be the first CETA trial that is specifically designed to evaluate the treatment effectiveness among an adolescent population and the first to feature a technology-based training modality and a telehealth delivery. This study is a first step to build a system of technology-driven training and treatment provision to expand access to evidence-based mental healthcare in Zambia and other LMIC settings. The need for effective, remotely delivered interventions is particularly relevant in the COVID-19 era.

There are several notable limitations to this study. First, this trial has a risk of social desirability bias in AYA reporting of symptoms, particularly in the CETA treatment arms given their therapeutic relationship with counselors. To combat this risk, we are using a standardized ACASI assessment system to measure symptoms at all time points, administered by research assistants and not by the counselors themselves. Second, this trial is occurring across several urban sites in the capital city of Zambia, and our participants will not be representative of AYA in more rural areas of Zambia and across other rural LMIC settings. Additional research will be needed on the delivery of these interventions to rural populations where T-CETA may actually be more feasible and acceptable because of access to private space and the high costs of transportation to a clinic.

If the CETA technology training platform is deemed feasible and comparably effective to in-person training models, and T-CETA is found to be as effective as in-person CETA for AYA in Zambia, we aim to expand these technology-driven, cost-effective training and treatment delivery methods across several contexts in sub-Saharan Africa and other LMIC globally.

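### The protocol says ACASI makes outcome assessment blinded, but the ACASI outcomes are self-reports by clients who know their arm; only the data analysts are blind

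*Protocol article*

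**What the plan says.** Under Randomization and blinding, the protocol article makes one positive claim about outcome assessment: "The use of ACASI will result in the outcome assessments being blinded". It adds that "data analysts will also be blind to the intervention status when conducting analyses".

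The same paragraph describes who knows the allocation:

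- Clients: "Eligible AYA clients will be informed immediately of the result of the randomization", and "neither counselors nor AYA clients will be blinded".
- Field staff: "At this point, the field staff will not be blinded to condition assignment for participants they assess".

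Under Screening and baseline assessment, ACASI is described as self-completion on a laptop with headphones. On staff presence the article says: "A research assistant will be positioned nearby in case the participant has any difficulty".

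Under Outcomes, the three primary outcomes are the CPSS trauma score and the YSR internalizing and externalizing scores, all given by ACASI. Substance use (ASSIST) and aggression/violence (Youth Victimization Scale) are collected the same way.

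The Discussion names social desirability bias as the first limitation and says that it applies particularly to the CETA arms. The stated countermeasure is standardized ACASI, "administered by research assistants and not by the counselors themselves".

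**The concern.** For a self-reported questionnaire, the respondent is the outcome assessor. Assessment is blinded only if the respondent does not know the arm, and here the respondent is told it. The paragraph therefore claims a property that its own next statements rule out.

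The superiority contrasts are most affected. They compare clients who know they were assigned CETA or T-CETA with clients who know they were not. If clients in the CETA arms tend to report fewer symptoms than they have, as the Discussion allows, that tendency is differential. It adds to the estimated effect and does not cancel.

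A report that carries the claim forward would describe these contrasts as resting on blinded assessment, and so credit them with a safeguard that the trial does not have. For T-CETA versus CETA, both groups know they are receiving the treatment, so the direction of any bias is less clear.

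**Working it through.** **Step 1: who is blind.** The claim rests on no figure, so the check sets the statements side by side.

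| Role | Knows the arm? | Where stated |
|---|---|---|
| Client, who answers every ACASI item | Yes | Randomization and blinding |
| Counselor | Yes | Randomization and blinding |
| Field staff, for those they assess | Yes | Randomization and blinding |
| Data analyst | No | Randomization and blinding |

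Each CPSS and YSR score is produced by someone in the first row. Self-completion takes the asking, rating and recording of answers away from staff. It does not change what the client knows. Of the four roles, only the analyst is blind, and the analyst works on scores already given.

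**Step 2: what self-report covers.** It covers the client outcomes given by ACASI, including all three primary outcomes. It does not cover counselor and trainer competency, fidelity and knowledge, which come from role-plays and knowledge tests, nor costs.

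**Step 3: an illustration of what unblinded self-report could do.** Inputs from Data analysis: SD 13, superiority alpha 0.025, power 0.80, effect 0.5 SD = 6.5 CPSS points, 78 per arm for superiority, and 114 per CETA arm for non-inferiority.

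The plan's superiority figure comes first. By normal approximation, n = 2 × (2.2414 + 0.8416)² / 0.5² = 76.04, so 77 per arm. A two-sided t-test gives 77.3, so 78, as stated. The alpha of 0.025 therefore behaves as two-sided, with 1.25% in the tail that favors CETA.

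With 114 versus 78 completers:

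- SE = 13 × √(1/114 + 1/78) = 1.910 points.
- Smallest significant difference = 2.2414 × 1.910 = 4.28 points.

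Suppose there is no true effect, and that reporting alone shifts the difference by b points in favor of CETA. The chance of a false claim is then P(Z > 2.2414 − b/1.910).

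| Assumed shift b | In SD units | Share of the 6.5-point effect | Chance of a false claim favoring CETA |
|---|---|---|---|
| 0 points | 0 | 0% | 1.25% |
| 1 point | 0.08 | 15% | 4.3% |
| 2 points | 0.15 | 31% | 11.6% |
| 2.6 points | 0.20 | 40% | 18.9% |

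The values of b are assumptions; the documents give none. The calculation is a simple two-group comparison, not the planned mixed model.

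**The case against.** The best defense is that nothing is hidden. The sentence right after the claim says that clients and counselors are unblinded, and the Discussion lists social desirability bias first among the limitations. ACASI is offered there to combat that risk, not to abolish it. The claim can also be read charitably: although field staff know the arm, they do not ask, rate or record the answers. That protection is real, and a careful reader has the facts needed to see through the label. Self-report by unblinded clients also follows from comparing in-person, telephone and usual care, so it is not a poor choice of design.

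Most of this stands. It makes the defect a wrong description, not concealment. It does not rescue the sentence, because neither the disclosure nor the limitation withdraws the claim, and the article nowhere says that outcome assessment is unblinded.

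A reader might infer more than the documents support:

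- *That every outcome in the trial is unblinded client self-report.* Role-plays, knowledge tests and costs are not.
- *That ACASI protects against nothing.* It limits interviewer and counselor influence, and analyst blinding is unaffected.
- *That TAU clients simply wait without contact.* Under Treatment as usual control, counselors check on their safety monthly, use of usual services is encouraged, and an adherence team serves all arms.
- *That the percentages above measure the error.* They depend on an assumed shift, and rewording the sentence changes none of them.

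**Conclusion.** The claim of blinded outcome assessment is wrong as written. It is contradicted within its own paragraph and by the self-completed mode of all three primary outcomes. This conclusion rests on the text alone and needs no assumption.

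The correct description is unblinded self-report, with reduced interviewer and counselor influence and blinded analysis. No sample size or other stated figure changes, and the trial's validity as a randomized comparison is not in question. What changes is how firmly the CETA and T-CETA versus TAU results can be stated.

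The size of any reporting bias is unknown. The range of about 4% to 12%, against a nominal 1.25%, holds only under an assumed shift of 1 to 2 CPSS points, SD 13 and 114 versus 78 completers. It shows why the label matters and does not measure the wording error.

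**What to change.** 1. Under Randomization and blinding, replace the ACASI sentence with: *Outcomes are self-reported by participants who know their assignment, so outcome assessment is not blinded; ACASI reduces interviewer and counselor influence, and only data analysts are blind.*
2. Say the same in the limitations in the Discussion and in the reporting of results.
3. Interpret the CETA and T-CETA versus TAU contrasts as unblinded self-report. Note that the direction of bias is less clear for T-CETA versus CETA.
4. Optional and secondary: where existing staffing allows, have follow-up ACASI sessions attended by a research assistant who has not been told the client's arm. This limits staff influence but does not blind the assessment, because the client still knows. The article gives no staffing numbers, so feasibility cannot be judged from it.

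Items 1 to 3 cost only wording. The downside is that the trial can no longer describe its outcome assessment as blinded.

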### Intervention arms

#### CETA

The Common Elements Treatment Approach (CETA) is a transdiagnostic, multi-problem intervention designed to address adult and youth trauma, depression, anxiety, safety, and substance use [75]. It comprised a small set of common elements found to be efficacious and prevalent across a range of EBTs to treat common mental health problems. CETA was designed to be flexible in the elements utilized, their order, and their dose (number of sessions) to allow counselors to address heterogeneity, comorbidity, and symptom fluctuations in and across clients. Treatment typically consists of 6 to 12 weekly, approximately 60-min sessions delivered by lay workers.

#### T-CETA

For the adaptation of the CETA manual for telephone delivery, we reviewed evidence-based telehealth strategies and recommendations, telehealth ethical and legal guidelines, and clinical recommendations from telehealth providers. In addition, local trainers-in-training in multiple contexts reviewed telehealth modifications and provided input that was incorporated into the final T-CETA manual used in this study. No changes were made to the structure, duration, and dose of CETA sessions, treatment components, or measurement-based clinical decision-making processes. Telehealth modifications, additions, and strategies were incorporated throughout the manual in delineated “telehealth boxes.” This way, the original manual was maintained outside of the telehealth boxes, allowing for clear identification and training of telehealth modifications for both new and existing CETA counselors. A pilot phase was conducted in Zambia to explore the feasibility and acceptability of T-CETA and to obtain feedback for modifying the telehealth additions or implementation strategies. Qualitative results highlighted the barriers to T-CETA treatment (i.e., poor connection; client phones off or not having phones; lack of private spaces) and solutions to these barriers (i.e., using community staff’s phone for sessions; obtaining multiple contacts for participants; home visits). For those with access to a telephone, T-CETA was deemed by participants as acceptable and effective.

##### Treatment as usual control

Participants randomized to the TAU condition will be encouraged to continue engaging with support services normally offered in their community, such as those provided by the partnering organization, and the types and utilization of these services will be tracked. Counselors will check in with TAU participants monthly to assess safety; any participant with a safety risk will be contacted by a counselor to complete a safety plan and be monitored. All TAU participants will receive a full course of CETA, if desired, after completion of the active study aims. For all study arms, a dedicated adherence team will be identified at each partner site and overseen by the project manager. Adherence strategies will include regular telephone check-ins, coordination with other site providers, and, if needed, home visits. Following the participation in the trial, participants will be provided a list of available resources in the community and the option to reengage with CETA providers in the area, if needed.

##### CETA training

CETA training and supervision activities in this study build on the existing apprenticeship model for lay providers to become mental health counselors [76]. In this model, the trainer initially assumes responsibility for teaching core skills and guiding the prospective counselor. After the initial training, supervisors, who may be identified beforehand or from the cohort of new counselors, are responsible for acting as the link between counselors and trainers. Before counselors begin delivering the intervention to clients, supervisors run practice groups with prospective counselors, which are then followed by supervision groups. Practice groups involve role-plays of a particular intervention component or skill, while supervision groups involve each prospective counselor going through one or two pilot cases with a supervisor who has previously piloted the case themselves with a trainer. When supervisors are providing guidance during practice and supervision groups to counselors, supervisors also engage in weekly calls with a trainer to receive consultation and support. At every level, each individual grows in their role over time and develops the necessary skills so that those who deliver coaching and support eventually provide minimal guidance. For this study, trainers-in-training (*N* = up to 6) will learn how to train new counselors and supervisors via the technology platform.

The technology-based TTT developed for this study consists of 10 days of trainers-in-training reviewing CETA components on the tech platform, expert CETA trainers modeling training components live via video chat and live and pre-recorded video observation of trainers-in-training role-plays by expert CETA trainers. Role-plays by trainers-in-training will be rated using a structured rating system, with feedback provided during live video sessions.

Following the TTT, groups of CETA trainers-in-training (pairs, or triplet groups) will each facilitate separate technology-delivered CETA training to the new prospective CETA counselors from our partnering organizations. Trainers-in-training will facilitate technology-delivered trainings to prospective counselors, which include training on standard CETA and T-CETA delivery. Each training will be conducted with approximately 25 counselors (*N* = up to 50).

### Outcomes

The primary outcomes in the trial will be AYA trauma symptoms (as measured by the CPSS), internalizing symptoms, and externalizing behaviors (both measured by the YSR) administered via ACASI as described in the “Screening and baseline assessment” section. Secondary outcomes among AYA, also administered via ACASI, include substance use, which will be measured with the Alcohol, Smoking, and Substance Involvement Screening Test (ASSIST) [67, 77] and aggression/violence as measured by the Youth Victimization Scale [78]. Outcomes are assessed at baseline, post-treatment completion (approximately 3–4 months post-baseline for TAU participants), and 6 months post-treatment completion (approximately 9 months post-baseline for TAU participants). The primary time point is post-treatment.

In addition to AYA outcomes, we will collect preliminary data on counselor and trainer competency, fidelity, and knowledge. This will be collected at various points throughout the study through standardized role-plays and CETA knowledge tests. Mixed methods interviews will be conducted among clients, counselors, and trainers to explore the acceptability and feasibility of CETA training and delivery. We will also collect data on health utility among AYA using the EuroQol 5-Dimensions for Youth (EQ-5D-Y) [79, 80] to inform the cost-effectiveness analyses. In all, AYA participants will be engaged in the study for approximately 9–12 months.

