**Methods:**

This study is a hybrid type 1 three-arm randomized trial to be conducted in Lusaka, Zambia. Following an apprenticeship model, experienced non-professional counselors in Zambia will be trained as CETA trainers using a remote, technology-delivered training method. The new CETA trainers will subsequently facilitate technology-delivered trainings for a new cohort of counselors recruited from community-based partner organizations throughout Lusaka. AYA with mental and behavioral health problems seeking services at these same organizations will then be identified and randomized to (1) in-person CETA delivery, (2) telehealth-delivered CETA (T-CETA), or (3) treatment as usual (TAU). In the superiority design, CETA and T-CETA will be compared to TAU, and using a non-inferiority design, T-CETA will be compared to CETA, which is already evidence-based in other populations. At baseline, post-treatment (approximately 3–4 months post-baseline), and 6 months post-treatment (approximately 9 months post-baseline), we will assess the primary outcomes such as client trauma symptoms, internalizing symptoms, and externalizing behaviors and secondary outcomes such as client substance use, aggression, violence, and health utility. CETA trainer and counselor competency and cost-effectiveness will also be measured as secondary outcomes. Mixed methods interviews will be conducted with trainers, counselors, and AYA participants to explore the feasibility, acceptability, and sustainability of technology-delivered training and T-CETA provision in the Zambian context.

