### Overview of study design

This study will use a hybrid type 1 three-arm parallel-group randomized controlled design [66] to compare the effectiveness of CETA delivered either in-person or via telephone (T-CETA), compared with a treatment as usual (TAU) control group. CETA trainers (up to *N* = 6) will be identified from an existing cadre of Zambian counselors and will be trained to be CETA trainers via a technology platform. They will be trained to facilitate technology-delivered CETA trainings to new prospective counselors (up to *N* = 50) recruited from our partnering organizations, who will be trained to deliver both in-person CETA and T-CETA. We will recruit and randomize AYA clients (*N* = 400) with mental and behavioral health problems from our partnering organizations to one of the following three conditions: (a) CETA, (b) T-CETA, or (c) TAU. We will evaluate mental and behavioral health outcomes among AYA at baseline, post-treatment (approximately 3–4 months post-baseline), and 6 months post-treatment (approximately 9 months post-baseline) (Fig. 1). Data will also be collected on CETA trainer and counselor competency, fidelity, and knowledge, and implementation constructs (e.g., acceptability, feasibility, cost) associated with training and intervention delivery.

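### The Outcomes section ties the primary visit to treatment completion and gives a calendar time only for TAU, so follow-up time can differ between the CETA arms and TAU

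*Protocol article*

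**What the plan says.** The protocol article describes the follow-up visits in two ways.

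- **Outcomes.** The first follow-up is at "post-treatment completion (approximately 3–4 months post-baseline for TAU participants") and the second at "6 months post-treatment completion (approximately 9 months post-baseline for TAU participants"). In both, the anchor is completion of treatment and the time since baseline is attached to TAU alone. The section adds: "The primary time point is post-treatment".
- **Abstract (Methods) and Overview of study design.** The same visits are given without distinction by arm: "post-treatment (approximately 3–4 months post-baseline), and 6 months post-treatment (approximately 9 months post-baseline").

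Scheduling in Randomization and blinding follows the first pattern. "TAU participants will be told that the study team will contact them in approximately 3 months to schedule their first post-assessment", whereas CETA and T-CETA participants are told only that a counselor will call within two days to arrange the first session.

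On treatment length, the CETA section says: "Treatment typically consists of 6 to 12 weekly" sessions of about an hour, with the number of sessions left flexible. The T-CETA section states that session structure, duration and dose are the same as for in-person CETA.

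Data analysis specifies an intent-to-treat approach and a mixed model with group, time and their interaction.

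**The concern.** Participants are enrolled because they score above a symptom cutoff, so scores can be expected to change with time in every arm, treated or not. If the CETA arms are assessed at one time since baseline and TAU at another, that background change enters the difference between arms along with the treatment effect. Randomization does not remove it, because the timing difference is created by the assigned arm.

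An anchor on completion is also not neutral. Treatment length is flexible and set in response to the client's presentation, so the date of the primary assessment may depend on the client's course in the active arms but not in TAU. In addition, the article names no visit date for an active-arm participant who does not complete, although the analysis is by intent to treat.

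At stake is the primary time point of the two superiority comparisons. Once visits have taken place at unequal times, analysis can only partly repair it.

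**Working it through.** **1. The plan's own figure.** Inputs from Data analysis: SD 13, effect size 0.5 (0.5 × 13 = 6.5 CPSS points), alpha 0.025 per comparison, power 80%.

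n per arm = 2 × (z₀.₉₈₇₅ + z₀.₈₀)² / 0.5² = 2 × (2.241 + 0.842)² / 0.25 ≈ 76.0, rounded up to 77. The t-test version gives 78, the stated figure. Two-sided alpha of 0.025 is therefore what the plan used. The timing question does not change this number.

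**2. When treatment ends if sessions run on schedule** (weeks × 7 / 30.44 days per month).

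- 6 weeks: 42 / 30.44 = 1.38 months
- 12 weeks: 84 / 30.44 = 2.76 months

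**3. Gap to TAU at the primary visit**, assuming the CETA visit follows the last session directly.

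- Smallest: 3 − 2.76 = 0.24 months
- Largest: 4 − 1.38 = 2.62 months

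In all on-schedule cases TAU is assessed later. Missed or postponed sessions shrink the gap and, beyond 4 months, reverse it.

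**4. Gap at the second follow-up**, on the same assumption (completion plus 6 months, against about 9 months in TAU).

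- Longest course: 9 − (2.76 + 6) = 0.24 months
- Shortest course: 9 − (1.38 + 6) = 1.62 months

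**5. What a shift would do (illustration only).** The bias is the background change per month times the gap in months. The document gives no rate of background change. An assumed range of 0.25 to 1.5 CPSS points per month, with gaps of 0.25 to 2.6 months, gives:

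- Low end: 0.25 × 0.25 = 0.06 points, or 1% of 6.5
- High end: 1.5 × 2.6 = 3.9 points, or 60% of 6.5

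For a shift of 1 point (for example 1 point per month and a 1-month gap), with 78 per arm, SE = 13 × √(2/78) = 2.08 and power = Φ(difference / SE − 2.241):

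| Situation | Apparent difference | Power |
|---|---|---|
| Equal timing | 6.5 | 0.81 |
| TAU assessed later, scores improving | 5.5 | 0.66 |
| CETA arm assessed later, scores improving | 7.5 | 0.91 |

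The gain in the last row is spurious. With no true effect and 114 against 78 participants, SE = 13 × √(1/78 + 1/114) = 1.91, and a 1-point shift raises the two-sided rejection rate from 0.025 to about 0.046.

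**6. Non-inferiority.** CETA and T-CETA have the same anchor and the same nominal duration. If their completion times are equal, the shift is 0.

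**The case against.** The strongest reply is that the article does name one target for all arms: the abstract and the design overview both say about 3–4 months with no exception. On that reading, the parenthesis in Outcomes only supplies a date for the arm that has no end of treatment and does not release the CETA arms from the target. The article never says that the visit follows the last session at once. Exact visit windows are the kind of detail an article leaves to the full protocol, which the Data Availability section says exists.

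Much of this stands. Unequal timing is a possibility that the wording allows, not something the document states. But the two descriptions differ on the anchor of the primary time point, and following Outcomes literally produces the gap in steps 3 and 4. That is a conflict in the published text, not a detail left out of it.

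Four stronger readings are tempting, and the document does not support them:

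- **That the arms will differ in timing and the result will be biased.** Neither size nor sign can be derived. If CETA clients are seen earlier and scores improve with time, the error runs against CETA.
- **That the non-inferiority contrast is biased too.** The pilot's connection, phone and privacy problems make slower T-CETA completion plausible, but the same section lists remedies and reports no delay.
- **That the model cannot adjust for timing.** Data analysis says only time; it does not say whether this is the visit or elapsed time.
- **That non-completers go unassessed.** The analysis is by intent to treat, and the Treatment as usual control section gives every arm an adherence team with check-ins and home visits. Only the visit date for these participants is unstated.

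**Conclusion.** The point holds in limited form. The anchor of the primary and second follow-up visits is inconsistent between the abstract and design overview on one side and Outcomes on the other. Taken literally, the Outcomes wording can put the primary visit of an on-schedule CETA client about 0.2 to 2.6 months before that of a TAU participant, provided the visit follows the last session directly.

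The exposed comparisons are CETA against TAU and T-CETA against TAU, in either direction. T-CETA against CETA is at risk only if actual completion times differ. The power figures rest on an assumed 1-point shift and show only that a modest timing effect would matter; they do not estimate the bias. Because the issue concerns the primary time point and is cheap to settle before data collection, it should be fixed, but it does not invalidate the design.

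**What to change.** Reconcile the abstract, the design overview and Outcomes by defining each follow-up in all three arms by one common window from randomization, using the times already named (about 3–4 months, and about 9 months). State that the visit takes place whether or not treatment was completed or started. Record the date of the last session descriptively. Add one sensitivity analysis with actual time since randomization in the model. If the full protocol already fixes such a window, aligning the Outcomes wording with it is enough.

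The cost is a change of visit wording and scheduling; no sample size changes. The small downside is that some active-arm participants are assessed some weeks after, or shortly before, their last session. For an on-schedule course the delay runs from 3 − 2.76 = 0.24 to 4 − 1.38 = 2.62 months. The primary contrast then describes the effect at a fixed time after randomization, not at the end of each client's treatment.
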